## Summary

**Background:** By expanding primary health care services, Ethiopia has reduced under-five mortality. Utilisation of these services is still low, and concerted efforts are needed for continued improvements in newborn and child survival. “Optimizing the Health Extension Program” is a complex intervention based on a logic framework developed from an analysis of barriers to the utilisation of primary child health services. This intervention includes innovative components to engage the community, strengthen the capacity of primary health care workers, and reinforce the local ownership and accountability of the primary child health services. This paper presents a protocol for the process and outcome evaluation, using a pragmatic trial design including before-and-after assessments in both intervention and comparison areas across four Ethiopian regions. The study has an integrated research capacity building initiative, including ten Ph.D. students recruited from Ethiopian Regional Health Bureaux and universities.

**Methods:** Baseline and endline surveys two years apart include household, facility, health worker, and district health office modules in intervention and comparison areas across Amhara, Southern Nations Nationalities and Peoples (SNNP), Oromia, and Tigray regions. The effectiveness of the intervention on the seeking and receiving of appropriate care will be estimated by difference-in-differences analysis, adjusting for clustering and for relevant confounders. The process evaluation follows the guidelines of the UK Medical Research Council. The implementation is monitored using data that we anticipate will be used to describe the fidelity, reach, dose, contextual factors and cost. The participating Ph.D. students plan to perform in-depth analyses on different topics including equity, referral, newborn care practices, quality-of-care, geographic differences, and other process evaluation components.

**Conclusion:** This protocol describes an evaluation of a complex intervention that aims at increased utilisation of primary and child health services. This unique collaborative effort includes key stakeholders from the Ethiopian health system, the implementing non-governmental organisations and universities, and combines state-of-the art effectiveness estimates and process evaluation with capacity building. The lessons learned from the project will inform efforts to engage communities and increase utilisation of care for children in other parts of Ethiopia and beyond.

Trial registration: Current Controlled Trials ISRCTN12040912, retrospectively registered on 19 December, 2017. http://www.isrctn.com/ISRCTN12040912

## Background

Ethiopia reached the Millennium Development Goal 4, reflected in a reduction of the under-five mortality from 205 deaths per 1000 live births in 1990 to 64 in 2014 (1). Neonatal mortality also decreased from 55 to 28 deaths per 1000 live births in the same period. The expansion of primary care services, improvements in nutrition (2), and progress across other sectors of society have reportedly contributed to reaching this goal. An analysis based on the Global Burden of Disease study reported neonatal conditions, together with lower respiratory tract infection and diarrhoeal diseases, as the dominant causes of under-five death (3).

As part of the Health Extension Program, in 2003 the Ethiopian Government introduced a new cadre of primary care workers called Health Extension Workers (HEWs)to reinforce efforts to improve maternal, newborn and child health in Ethiopia (4). This category of health workers is reportedly able to correctly manage multiple child illnesses through the integrated community case management (iCCM) activities that the government initiated in 2010 (5). If appropriately trained and supported, this cadre can also treat severe infections of the newborn in a cost-effective way within the Community-Based Newborn Care (CBNC) program that has been running since 2014 (6). Although nearly all the HEWs throughout the country have been trained, relatively few sick newborns have been identified and treated(7). Since 2011 a volunteer cadre called the Women’s Development Army (WDA-also known as the Health Development Army or Women’s Development Group) is active in promoting the use of health services (8,9). There are two levels to the WDA leaders. The smaller unit is comprised of 6 women, with one serving as a leader. Five or six of these networks are combined to form a group. The approximately 30 women in one group are led by one of the network leaders. The WDA leaders work closely with HEWs to promote maternal and child health services.

In Ethiopia, the utilisation of maternal health services shows disparities between regions and social groups (10,11), and skilled birth attendance, although increasing, has remained inadequate with increasing social inequity (12). Insufficient number of sick children are taken to HEWs for treatment of common childhood diseases, and the expansion of the iCCM program has not created sufficient community demand for use of these services (13).

The low utilisation of child health care calls for concerted efforts to improve the equitable reach of high-quality services (14,15). This background formed the rationale for developing a complex intervention to engage the community, strengthen the capacity of primary care workers to provide high-quality services and reinforce the local ownership and accountability of the primary level maternal and child health services. It was hypothesized that, given the low service utilization, increased awareness and promotion of primary health services in combination with strengthened provision of iCCM and CBNC and improved ownership and accountability of these services would lead to increased service use, which ultimately would further reduce neonatal and under-five mortality.

Thus, the evaluation described in this protocol aims to assess whether the proportion of children under the age of five years with suspected pneumonia, diarrhoea, fever or neonatal sepsis, that seek and receive appropriate care has increased in intervention as compared to comparison areas. Further, we present a plan for whether the information on the fidelity, reach, and dose of the interventions support the plausibility of changes in the outcome, and provide insights into the pathways of effects, feasibility, and program cost-effectiveness. Findings of this evaluation will be used to improve existing platforms of service delivery in the country. It is anticipated that successful interventions will be scaled up nationally provided sufficient budget support is available.

## Design and methods

### Setting

The Federal Ministry of Health in collaboration with the non-governmental partners UNICEF, Last 10 Kilometres/John Snow, Inc., Save the Children, and PATH initiated the “Optimizing the Health Extension Program” project to increase the utilisation of primary child health services. This evaluation has a pragmatic trial design with purposefully selected 26 intervention and 26 comparison districts (woredas), with a total population of 8 million, across four regions of Ethiopia (Amhara, Southern Nations Nationalities and People, Oromia, and Tigray). Figure 1 shows the intervention and comparison areas within these four regions.

[figure not shown]

Figure 1. Map of Ethiopia showing all regions (left) and the intervention and comparison districts within the four study regions (right).

The intervention areas are selected by government and implementing partners for having a relatively low utilization of primary child health services. The Regional Health Bureaus in these regions, with the support from their local universities, will select the comparison districts to match the intervention districts. Selection is based on demographic and health criteria that includ population size, number of primary health care units, burden of diseases, health service performance data, length of time since iCCM and CBNC program initiation, prior exposure to other similar programs, and absence of non-governmental organizations addressing demand generation. The intervention, which will start in 2016, has an intended duration of 2.5 years and is based on an analysis of barriers to the utilisation of newborn, child and maternal health services. The planned evaluation follows a plausibility approach (16). It includes analysis of difference in differences of outcomes and a process evaluation of the intervention in line with the UK Medical Research Council’s guidelines (17).

The baseline and endline surveys, as well as the process evaluation are implemented by the London School of Hygiene & Tropical Medicine (LSHTM) and Ethiopian Public Health Institute (EPHI) along with representatives from Gondar, Jimma, Mekelle and Hawassa Universities. A steering committee comprising representatives from each of the universities, implementing partners, Ethiopian Public Health Institute and Federal Ministry of Health will be established to meet quarterly. The committee will provides advice on the evaluation of the project and assists in resolving issues encountered during the course of the evaluation. Given that the Optimising the Health Extension Program is a community and health system level intervention, a data monitoring committee is not deemed necessary.

### Barrier analysis

Key Ethiopian governmental and non-governmental stakeholders in the field of maternal, newborn and child health services met in 2016 for a facilitated workshop where the perceived demand- and supply-side barriers to CBNC and iCCM service utilisation were identified. The demand-side barriers included perceived lack of knowledge of diseases and danger signs (18), and lack of awareness of what primary level services could offer. Further, it was suggested that families often have a preference for traditional healers and home remedies (19) and that the higher availability of services offered by private providers was also appreciated in the households (20). In a qualitative analysis of barriers to care-seeking for common childhood infectious diseases, the trust in the primary care services was low (21). The barrier analysis showed a lack of community awareness of the curative, as well as preventive services provided by the HEW and that the quality of care on the primary level was perceived to be low (22). Also, there was a felt need to strengthen the HEWs in supporting pregnant women in birth preparedness, referral to midwives, and institutional delivery (23). All the above listed barriers resulted in under-use of maternal, newborn and child health services. Other demand side barriers included delay in seeking care due to the need to obtain husbands’ permission and financial support, the perceived cost and real cost of travel, particularly due to costs associated with referral of severely ill children to a further facility and repeated travel due to health post closure (21). Supply-side barriers included frequent stock-outs of medicines and other necessary supplies, service interruption and inconsistent operating hours at health posts (24). Further, it showed that HEWs had poor skills and confidence (25), especially when managing and treating newborns (26), lack of local government ownership and lack of accountability for both the CBNC and iCCM programs, and inconsistent supervision and monitoring. This barrier analysis formed the basis of a logic framework for a complex intervention that postulated that community engagement would increase care seeking for ill children, capacity building would improve availability of quality of CBNC and iCCM services and district level ownership and accountability would improve integration of these services into the district level planning and budgeting (Table 1). Together these three strategies would lead to an increased utilization of CBNC and iCCM services.

Table 1. Logic framework for the Optimizing Health Extension Program intervention in selected districts of Ethiopia.

| Assumptions | - Local stakeholders committed to coordinate and support the interventions - Traditional leaders will promote the maternal, newborn and child health services - The government health sector and supply chain partners will ensure drug and service availability | | |
| --- | --- | --- | --- |
| Strategies | COMMUNITY ENGAGEMENT | CAPACITY BUILDING | OWNERSHIP, ACCOUNTABILITY |
| Interventions | - Health post open house - Group discussions led by Women’s Development Army (WDA) members - Reaching male partners - Engaging schools - Engaging religious and traditional leaders - Health films - Radio spots and dramas | - WDA level one training - Community-based data for decision making - Health Extension Worker (HEW) gap filling training and job aids - Supportive supervision of HEWs - Performance review and mentorship meetings with HEWs - Provision of job aids and tools | - Advocacy for the integration of Community-Based Newborn Care (CBNC) and integrated community case management (iCCM) into planning, budgeting, management, and information systems of the district and sub-district levels. - Management standard for health post opening hours - Ambulance service for children’s referral - Engage Kebele (sub-district) command post in the efforts   Establish community feedback mechanism |
| Output | - Awareness of childhood illness and availability of CBNC and iCCM - Acceptance of health post care - Evidence-based social and behavioural change communication | - WDA members capacitated - HEWs gained skills - Supportive supervision and performance review and mentorship meetings with HEWs done | - CBNC and iCCM integrated in the planning, management and information systems at district and sub-district levels - Standard set for health post opening hours - Sub-district level local administration engaged in demand creation and support to primary health service provision - Community feedback mechanisms created - Advocacy to decision makers and influential bodies |
| Intermediate outcomes | - Improved child health practice at household and community levels   Data source: Household module   - Improved availability of high quality community-based newborn care and integrated community case management of childhood diseases   Data source: Health post, health extension worker and health provider assessment module   - Improved ownership and accountability of community-based newborn care and integrated management of childhood illnesses   Data source: woreda contextual factors module | | |
| Outcome | - Increased utilisation of good quality community-based newborn care and integrated management of childhood illnesses   Data source: household module | | |
| Impact | - Reduction of under-five mortality | | |

### The intervention and underlying assumptions

The package of interventions to be implemented across 26 districts includes three interlinked strategies with possible synergies: (1) community engagement activities that aim at increasing the awareness of newborn and child diseases, the recognition and acceptance of the care provided on the primary level, and the formulation of action plans at the local level; (2) capacity building of HEWs and WDA leaders such as gap filling training, supportive supervision and mentorship to improve iCCM and CBNC services, and (3) strengthening the local government’s ownership and accountability of the primary newborn and child health services by advocating for the sustained integration of CBNC and iCCM into the planning, budgeting, monitoring, management and support systems of the district and sub-district level (Table 1). Assumptions made by the implementers to achieve the success of the Optimizing the Health Extension Program included support from local stakeholders, traditional and religious leaders, governmental health sector and supply chain partners.

### Implementation

The Ethiopian Government, in collaboration with PATH and UNICEF (through sub-contractors Save the Children and Last 10 Kilometres) will implement the intervention. These organizations will have quarterly meetings to harmonize the intervention activities across the 26 intervention districts.

Trained professionals from the implementing organizations and the public sector will facilitate the community engagement activities (Table 1). To raise community awareness of iCCM and CBNC services, implementers will organise health post open house sessions to introduce available services and conduct workshops with schoolteachers and religious leaders. Community engagement will also be supported by behaviour change communication materials (brochures, posters, and banners). Educational films developed by implementers will be screened in health facilities and similarly radio messages and dramas will be developed and broadcast in implementation districts. Health professionals within the district health services facilitate the capacity building activities. For example, midwives from health centres provide training to HEWs, while HEWs provide training for WDA leaders. Where missing, implementers will provide registration books, iCCM and CBNC treatment algorithm booklets and backpacks to carry these items for community level service provision. Facilitators from the implementing partners lead the ownership and accountability activities. District ownership efforts include advocacy workshops at district and sub-district levels and support to the annual district health planning sessions.

The implementers plan to achieve a high reach of the different innovations across all intervention districts. Thus, the ambition is that the community meetings, school engagement activities, training of WDA leaders and HEWs, as well as district ownership efforts should reach all areas and relevant stakeholders.

### Process evaluation, including mechanisms of impact, and contextual factors

The process evaluation is guided by the UK Medical Research Council framework for complex interventions (17). A graphical representation of the process evaluation is provided in Figure 2.

[figure not shown]

Figure 2. Framework for the process evaluation of the Optimizing the Health Extension Program intervention.

The implementing partners will prospectively collect data on the implementation of the interventions. The innovations within the three strategies will continually be harmonized across the implementing partners. Some variations between implementers and geographies is intended due to the different contexts of the districts. Such variations can be captured through the process evaluation. Implementers will also make efforts to harmonize the corresponding data sources. These databases will include information on each performed activity, including information on the innovation, the facilitator(s), the recipients, the health-system level and place, and timing of each activity. The implementing partners will also provide information on training and support to deliver the interventions and any changes made in some parts of the intervention districts or across all districts. This information will be aggregated to describe the fidelity (whether an intervention was delivered as intended), reach (how much of the intended audience was exposed to the intervention), and where feasible the dose (how much of the intervention was received by the intended audience) and adaptations (originally unintended changes made to an intervention across all or in selected parts of the study areas). In the endline survey, the participants (mothers of children below the age of five years, WDA leaders, HEWs, woreda health office representatives) will be asked about their contact with the interventions to measure reach. The baseline and endline surveys include questions on the interactions between the households and both WDA members and HEWs to measure dose (Table 2). Overall, the implementation process data will allow for analyses of whether the Optimizing the Health Extension Program innovations were implemented according to plans and associated with better awareness and acceptance of CBNC and iCCM services, provision of improved quality of services, and strengthened ownership and accountability of CBNC and iCCM services, respectively. In addition, a qualitative study will be conducted to explore views and experiences of program planners, managers and implementers, identifying what components worked well and what was not successful in the delivery of Optimizing the Health Extension Program interventions.

### Effectiveness of the Optimizing the Health Extension Program

The baseline and endline surveys in intervention and comparison areas will include modules for household, facility preparedness to provide child health services, the health worker, a quality of care assessment, the WDA leader and woreda contextual factors questionnaires. As part of the endline survey the HEWs will be interviewed, using the questionnaire-based Context Assessment for Community Health (COACH) tool (27). This validated tool measures eight aspects of the context in which the HEWs work.

Table 2. Baseline and endline survey questionnaires for the Optimizing the Health Extension Program intervention evaluation.

| Questionnaire modules | Content |
| --- | --- |
| Household  **N=6000** | - Location of household using global positioning system (GPS) coordinates - Members of household - Characteristics of the house and assets ^a^ - Women of reproductive age - Birth history - Use of maternal and perinatal health services - Knowledge of child diseases and danger signs - Care seeking and treatment for child illness - Preventive behaviour |
| Health post module  **N=200**  Halth centre module^b^ | - Location of health post and health centre using GPS coordinates - Facility-level preparedness to provide child health services - Data extracted from registers - Supportive supervision and mentorship from health centres to health posts |
| Health extension worker module **^c^** | - Knowledge on newborn and child health care - Training, supervision, mentorship - Services provided to newborns and children |
| Health centre staff module ^d^ | - Knowledge on newborn and child health care - Training, supervision - Services provided - Working conditions |
| Health provider assessment of the quality of care for a sick child module  **N=800** | - Observation and re-examination of Health Extension Workers’ assessment, classification, and treatment of sick children at health post |
| Women’s development army module  **N=200** | - Training - Knowledge - Activities in promoting maternal, newborn, and child health |
| Woreda contextual factors module  **N=52** | - Demography - Maternal, newborn and child health programs - District resources and infrastructure - Training and supervision activities, - Recent epidemics and natural disasters |
| Context Assessment for Community Health (COACH) module ^e^  **N=200** | - Available resources, - Community engagement, - Monitoring services for action, - Sources of knowledge, - Commitment to work, - Work culture, - Leadership, - Informal payment |

^a^ Asset ownership will be used to estimate relative socio-economic status, using an asset index based on principal components analysis

^b^ Some health posts are served by the same health centre hence the exact samples size can’t be determined

^c^ All the health extension workers in each health post will be interviewed. Due to the varying numbers of workers in health posts, the exact sample size can’t be determined.

^d^ We will interview one staff per sampled health centre

^e^ Conducted at endline survey only with on HEW in each health post

### Outcomes

*The primary outcome* is care seeking (at health posts, health centres, hospitals and clinics) for an illness in under-fives. *Secondary outcomes* include appropriate treatment for diarrhoeal diseases (oral rehydration therapy, zinc tablets), probable pneumonia (antibiotics), fever and malaria, and neonatal sepsis (antibiotics); improved knowledge towards childhood illnesses and treatment services among caregivers of under-5 children; improved attitudes or perceptions towards the iCCM and CBNC services at health posts; improved iCCM and CBNC program ownership by the public health sector (including inclusion of iCCM and CBNC indicators in their planning and budget allocation); and, improved availability of quality iCCM services provided by the HEWs.

*The sample size* for baseline and endline surveys is based on the requirement that these surveys should have adequate power to measure changes in a fixed number of percentage points between intervention and comparison areas from start to end of the study. For the household survey, the sample size was powered for the main outcome of care seeking for any illness in the two weeks prior to the survey. Sampling 30 households in the 100 selected enumeration areas would yield 3000 households per group. The Ethiopia Demographic Heath Survey (DHS) data has shown that the rate of children under-five to households surveyed was 0.65. Based on this assumption, a sample survey of 3000 households per group would be expected to achieve a sample size of 1747 children below the age of five years. The evaluation of the integrated management of childhood illness in Tanzania reported 50% of under-five children to have had an illness in the two weeks prior to the survey (28). We assumed a more conservative 30%. Based on the calculations of a sample size of 3000 households per group (6000 in total) with 90% completeness and a design effect of 1.3, we would have 80% power to detect differences of 10-20 percentage points across the range of child health indicators as statistically significant at the 5% level.

For the survey to assess the quality care provided by HEWs, with the assumption that each of the sampled enumeration areas will be served by one health post, the survey will include 100 intervention and 100 comparison area health posts for the quality of care assessment, where in each health post, the HEWs’ assessment of four sick children mobilized to come to the health post will be observed, followed by a re-examination of the child by a health officer. This will yield a sample size of 400 children in each group. A total of 800 children, with a design effect of 1.4, will have 80% power to detect a minimum of 15 percentage point changes in the correct classification of iCCM illnesses between intervention and comparison area HEWs at baseline and endline as statistically significant at the 5% level.

*The questionnaire tools for baseline and endline surveys* were adapted from the team’s own, and others’ previous work on the Integrated Management of Childhood Illness (28), iCCM (29), and CBNC (30). The questionnaire instrument includes modules regarding household, health posts and health centres, HEWs, health centre staff, WDA members, an observation and re-examination of the HEW assessing sick children, and district contextual factors (Table 2).

*The baseline and endline surveys* will be conducted in intervention and comparison areas to assess the situation before the intervention. A two-stage stratified cluster sampling will be applied in these two surveys using lists of enumeration areas of the 52 intervention and comparison districts from the latest (2007) Ethiopian census as the sampling frame. In the first stage, a list of all enumeration areas of the study districts will be based on the 2007 Ethiopian Housing and Population Census. Two hundred enumeration areas will be selected from 52 districts with probability proportional to size. Each enumeration area will form one cluster, and these clusters will constitute the primary sampling unit. In the second stage, a systematic random sampling technique will be applied to select 30 households in each cluster. All women aged 13 to 49 years who live in the selected households will be included, in order to identify women who had a live birth in the 12 months prior to the survey to assess care seeking in the neonatal period. Furthermore, children under the age of 5 years will be included to assess care seeking for any illness in the two weeks prior to the survey. For every cluster, the WDA leader serving the cluster will be interviewed. The health post and the HEWs serving the selected cluster, the health post’s referral health centre, and staff, and the district health office providing support to the selected facility will be approached with survey modules. All study participants will be sampled without replacement. Up to three visits will be made to each participant to maximize their inclusion into the study.

To evaluate the quality of assessment and care provided to sick children at the health posts, an observation of a sick child consultation with an HEW and a re-examination by a child health officer will be performed. Given that very few sick children are brought to the health post each day, data collectors will mobiliz the community to bring sick children on the day of the survey to ensure the required sample size is met.

Data collection teams and supervisors will be trained over the course of ten days. They will not be provided information on whether a district is an intervention or comparison area. Data will be collected on tablets and encrypted data will be regularly sent from the field to the Ethiopian Public Health Institute’s central server. The data manager will then decrypt the data and rigorous quality checks will be conducted with feedback to the field teams. Data cleaning will involve checking for errors, completeness and consistency. The data manager will also ensure that all standards for data security, curation and access were met.

*The effectiveness assessment* will be based on a plausibility design (16), analysing difference-in-differences of the primary and secondary outcomes (31). Data on primary and secondary outcomes will be analysed from baseline and endline household, health post, and health centre surveys in intervention and comparison districts, with adjustment for the cluster sampling and relevant confounding factors. The assessment will use blinded analysis. The code identifying the intervention and comparison areas will be revealed after the analysis and interpretations are completed.

Ten Ph.D. students from four Ethiopian universities, including candidates from the Regional Health Bureaus in the study provinces, and from the Ethiopian Public Health Institute, are engaged in the evaluation. PhD students will be involved in the conduct of the surveys, participating in the training of data collectors and serving as regional survey coordinators. They have chosen topics for in-depth sub-studies linked to the evaluation, including equity in the utilisation of services; spatial analyses of care utilisation; quality of care provided by the HEWs; the role of WDA leaders in promoting the use of services; newborn care practices; the referral of sick children; and focused studies of care utilisation for diseases of the newborn and diarrhoeal diseases. Most of the students plan to use baseline and endline surveys for quantitative data and to perform qualitative studies within their chosen topics.

Findings from the effectiveness study, process evaluation and PhD research will be published as scientific articles and reports. No professional writers will be used. Publications arising from this evaluation will follow the recommendations from the International Committee of Medical Journal Editors (32).

The interventions started in the 4^th^ quarter of 2016 and will run up to the end of 2018. Baseline survey will be conducted in the 4^th^ quarter of 2016 and endline survey will start immediately thereafter the end of the program implementation. Data for process evaluation collection and analysis will take place until September 2019. Data analysis for the effectiveness study will be performed from mid of 2019 onwards.

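### The 80% power claim for 10-20 points on all child health indicators is supported only for any-illness care seeking, and neonatal sepsis treatment falls short of it at assumed case shares up to 30% of births

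*Protocol*

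**What the plan says.** All of this is in the Protocol, Design and methods, Outcomes.

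- **What the survey is sized for.** The household survey is sized for the main outcome, care seeking for any illness in the preceding two weeks. The chain of inputs is: "Sampling 30 households in the 100 selected enumeration areas would yield 3000 households per group"; "the rate of children under-five to households surveyed was 0.65"; so the survey "would be expected to achieve a sample size of 1747 children below the age of five years". Two-week illness is taken as 30%, completeness as 90% and the design effect as 1.3.
- **What is then claimed.** The paragraph concludes that there would be 80% power to detect "differences of 10-20 percentage points across the range of child health indicators as statistically significant at the 5% level".
- **Which indicators exist.** The secondary outcomes include appropriate treatment of diarrhoea, probable pneumonia, fever and malaria, and "neonatal sepsis (antibiotics").
- **Where newborn data come from.** Women of reproductive age in sampled households are listed "to identify women who had a live birth in the 12 months prior to the survey to assess care seeking in the neonatal period".
- **How the outcomes are analysed.** The effectiveness paragraph applies DiD to primary and secondary outcomes alike. The sample size paragraph also frames its target as change between areas from the start to the end of the study.

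The protocol gives no expected number of cases, prevalence or baseline treatment rate for any single condition, and no expected number of births.

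**The concern.** A treatment outcome is measured only in children who had the condition, so its denominator is a subset of the ill children on whom the calculation rests. For neonatal sepsis it is a subset of one year's births. The power statement carries the any-illness result over to these smaller denominators without calculating them.

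Neonatal sepsis is named in the protocol's aim (Background), community-based newborn care is one of the two programmes being strengthened, and the findings are meant to inform scale-up. If a non-significant result for sepsis treatment is read against a stated 80% power, it could be taken as evidence of no benefit when the survey had little chance of showing one.

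**Working it through.** **Inputs from the protocol:** 3000 households per group, 0.65 under-fives per household, 90% completeness, 1747 under-fives, 30% ill, design effect 1.3, 80% power, 5% significance.

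**Assumptions:** two-sided testing; independent survey rounds; equal cell sizes; three cells at baseline rate p and one shifted to p + d; baselines of 10-50%; one design effect for all outcomes; births equal to one fifth of under-fives; sepsis case shares of 10-30% of births.

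**Step 1: reproduce the protocol's figures.** 3000 × 0.65 × 0.90 = 1755, against 1747 stated. Ill children: 1747 × 0.30 = 524 per group per round; effective number 524/1.3 = 403.

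The detectable DiD solves d = 2.80 × √{[3p(1−p) + (p+d)(1−p−d)] / n_eff}, where 2.80 = 1.96 + 0.84. With n_eff = 403, d is about 12 points at p = 20%, 13 at 30%, and 14 at 40-50%. A two-group comparison at one round gives 8.5-9.9 points. For any illness the stated range is therefore reproduced.

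**Step 2: cases needed for a 20-point DiD,** the loosest end of the claim. n = 2.80² × [3p(1−p) + (p+0.2)(0.8−p)] / 0.2² × 1.3, with 2.80² = 7.85 before rounding.

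| Baseline p | Bracketed term | Cases per group per round | Share of 1747 under-fives | Share of 349 births |
|---|---|---|---|---|
| 10% | 0.27 + 0.21 = 0.48 | 122 | 7% | 35% |
| 20% | 0.48 + 0.24 = 0.72 | 184 | 11% | 53% |
| 30% | 0.63 + 0.25 = 0.88 | 224 | 13% | 64% |
| 40% | 0.72 + 0.24 = 0.96 | 245 | 14% | 70% |
| 50% | 0.75 + 0.21 = 0.96 | 245 | 14% | 70% |

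**Step 3: diarrhoea, pneumonia, fever.** Applying the Step 1 formula at assumed prevalences among under-fives gives a detectable DiD, over baselines 10-50%, of:
- 20% prevalence (349 cases): 11-17 points
- 15% (262 cases): 13-19 points
- 10% (175 cases): 17-24 points
- 7% (122 cases): 20-28 points
- 5% (87 cases): 24-33 points

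A common condition meets 20 points; one at 5% or less does not.

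**Step 4: neonatal sepsis.** Births per group: 1747/5 = 349, about 350. Detectable DiD over baselines 10-50%:

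| Assumed share of births | Cases | Design effect 1.3 | Design effect 1.0 |
|---|---|---|---|
| 10% | 35 | 39-49 points | 34-44 points |
| 20% | 70 | 27-36 points | 24-32 points |
| 30% | 105 | 22-30 points | 19-27 points |

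With 35 cases and a true 20-point DiD, power is Φ(0.20/SE − 1.96), where SE = √(bracketed term × 1.3/35). This is 32% at a 10% baseline and 18% at 50%, against the 80% claimed.

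**Sensitivity.** Leaving out the 90% completeness gives 3000 × 0.65/5 = 390 births. Then 122/390 = 31% of newborns would still be needed at a 10% baseline, and 245/390 = 63% at 40-50%.

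**The case against.** The protocol says plainly that the household survey is powered for the main outcome, and a trial need not be powered for each secondary outcome. Its illness assumption of 30% is also deliberately below the 50% it cites. All of this stands: the primary sample size is not in question. But the power sentence reaches beyond the main outcome in its own words, so the fault is a positive statement that the inputs do not carry, not a detail left to a later document.

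A reader might infer that the claim must fail for every condition-specific outcome. The documents do not support that. They give no prevalences, one child can have several conditions at once, and the rationale of low service use may mean low baselines, where fewer cases are needed.

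A reader might also infer that about 350 births make the claim impossible for newborns. They do not by themselves: if all 350 formed the denominator, a DiD of 11-17 points would be detectable. The limit is the number of sepsis cases, which the protocol does not state.

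Finally, a design effect of 1.3 may be too high when about 35 cases are spread over 100 clusters. This lowers the figures but does not bring a 10% or 20% case share within 20 points at baselines of 10-50%.

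**Conclusion.** The 10-20 point, 80% power statement holds for any-illness care seeking (about 12-14 points by DiD at baselines of 20-50%). For diarrhoea, pneumonia and fever treatment it is unsupported but not shown to be false: each condition would have to affect about 7-14% or more of under-fives, depending on its baseline treatment rate.

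For neonatal sepsis treatment it is not attainable at design effect 1.3 for case shares up to 30% of births and baselines of 10-50%; at a 30% share the detectable DiD is still 22-30 points. This rests on the assumed number of births and case shares, neither of which is in the protocol. The exceptions lie at the edge: at a 30% share, the detectable DiD falls to about 18 points if the baseline is only 5%, or to about 19 points at a 10% baseline with no design effect. The conclusion is therefore that the claim is out of reach over this range, not that it is impossible in every case.

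**What to change.** - Limit the 10-20 point, 80% power statement to any-illness care seeking, and to any condition whose expected cases per group per round reach the required number (about 122 at a 10% baseline, rising to 245 at 40-50%). State the prevalence and baseline assumed for each condition so included.
- State that neonatal sepsis treatment is not powered for 10-20 points, will be reported as an estimate with a confidence interval, and that a non-significant result will not be read as no effect.

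The cost is a change of wording and a less favourable stated figure. No sample is added, and the primary outcome and its analysis are unchanged.
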